### **Secondary Outcomes**

Secondary outcomes will include behavioural changes in the life of people with AD and the changes that occur in the brain. For secondary outcomes the music group will be compared to the training group and both will be compared to the control group on all measures. The following is a list of secondary outcomes and which tests will be used to investigate them.

## **Secondary Behavioural Outcomes**

Title: Living independently at home

Description: A measure of when people with AD move to a nursing home

Time frame: 12 months (or longer)

Test: After 12 months of intervention we will ask our participants if they are still living at home or at a nursing home. We will also follow up with them after two and a half years and after five years to ask the same question. This is to get a deeper understanding of the longterm effects that music or exercise intervention may have on people with AD.

Title: Geriatric Depression Scale (GDS)

Description: Total score changes in the GDS which is a self-reported scale

Time frame: Testing before randomisation and after 12 months of intervention.

Test: GDS is a recognised test that is often used in psychological contexts and in research to gain and understanding of participants depressive symptoms or if they have depression. Depression is very common among the elderly. The GDS total score is the sum of 15 items, each of which is answered as yes (1) or no (0), the total score can range from 0 to 15. Higher scores indicates more severe depression symptoms. A score of > 11 indicates depression, with a sensitivity of 84 % and specificity of 95 %. However, for patients diagnosed with dementia (Burke, Houston, Boust, & Roccaforte, 1989), sensitivity and specificity has a somewhat lower cut-off score, which means that the test can only be used on people with light dementia, such as AD patients in early stages of the disease.

Title: Language abilities

Description: Word Learning Test

Time frame: Testing before randomisation and after 12 months of intervention.

Test: Language is one of the functions people with AD lose, and who often get worse with the disease. We want to see if our participants experience a recovery or not a deterioration through the intervention. Of course, this can also contribute to the effect of socialisation on a weekly basis, and that language is better taken care of by oral and interpersonal interactions. The reason we want to look at several parameters is to get an overview of what may be the different causes of change in the intervention.

Title: Sensor-motor functions

Description: Total score of the finger tapping test (FTT)

Time frame: Testing before randomisation and after 12 months of intervention.

Test: Sensor motor functions can be modified by intervention simply by stimulating work memory or focusing attention on participants during certain periods. Here we want to get a holistic impression of what is being changed and checking for other factors.

Title: Living independently with Alzheimer

Description: Alzheimer Daily Living Assessment (P-IADL) and total score of the Instrumental Activities of Daily Living (I-ADL).

Time frame: Testing before randomisation and after 12 months of intervention.

Test: We want participants who are in an early stage of Alzheimer's disease because we believe that music therapy can have a strong effect on those who can prevent the disease from developing. Therefore, we want to test the course of illness before and after interventions. Each of the eight

items is scored from one to three, four or five, for a total score ranging from 0 to 31. 0 is a none score, as it means not able to answer the questions. For example if the patient does not use medication, the score is 0, because there is no use to know if they can take it themselves. Low scores indicates high instrumental activities of daily activities, high score indicates little instrumental activities. For the other test, the total score ranges from 0 to 30. Low scores indicate high independence, while high scores indicate low independence.

Title: Memory and attention

Description: Total score of Mini-Mental State Examination (MMSE)

Time frame: Testing before randomisation and after 12 months of intervention.

Test: Memory and attention are two of the things that may be marked very early in AD, or that is why it is discovered. MMSE is commonly used in many Alzheimer's research and provides an idea of disease progression, as well as the ability to remember and learn. High score, or maximum score of 30 points indicates good mental state, while low scores (minimum 0) indicate poor mental state.

Title: Cognition

Description: Stroop test (online version)

Time frame: Testing before randomisation and after 12 months of intervention.

Test: Stroop test is a difficult cognitive test that challenges language, cognition and motor functions. We would like to use this test to look at cognitive abilities in people with AD. The digital version of the test presents one colour and participants are asked to name the colour. In half the trials a word is written in the colour participants are supposed to name. This is harder as the words are other colours, such as blue, red, yellow and green (these are also the colours participants must name correctly). Score is derived digitally based on correct trials, times and higher score for matching words and wrong colours, such as **blue**. High score indicates high cognitive functions.

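### The I-ADL total adds zeros for items that do not apply or cannot be answered to a scale on which low means independent, so an unrated item counts as better than full independence

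*Protocol*

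**What the plan says.** The outcome is in the protocol, Secondary Behavioural Outcomes, under the title on living independently with Alzheimer. It uses two instruments, one of them the I-ADL total. The scoring text fixes four things.

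- **Item and total range.** Each of the eight "items is scored from one to three, four or five, for a total score ranging from 0 to 31".
- **Meaning of 0.** "0 is a none score, as it means not able to answer the questions".
- **Example of a 0.** "For example if the patient does not use medication, the score is 0". The reason given is that the item does not apply to such a patient.
- **Direction.** "Low scores indicates high instrumental activities of daily activities, high score indicates little instrumental activities".

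The assessment times are given as: "Testing before randomisation and after 12 months of intervention". The section Secondary Outcomes adds: "For secondary outcomes the music group will be compared to the training group and both will be compared to the control group on all measures". Under Statistical Methods, outcomes other than the two primaries are exploratory and are tested at an unadjusted two-sided 5% level. No rule in the protocol removes, prorates or imputes items coded 0.

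**The concern.** A code that says no rating was obtained has been placed at the favourable end of the scale, below the best rating of 1. Two different situations share it: the item does not apply, and the participant cannot answer.

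In a 12-month trial in Alzheimer disease, either can arise between baseline and follow-up. Participants who move to a nursing home stay in the trial (Eligibility Criteria), and the activity questions are put to the participant in an interview (Appendix D, ADL). If an item rated at baseline becomes a 0 at 12 months, the total falls and the record shows better function. At stake is whether a change in this total, or a difference in it between arms, can be read as a change in independence.

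**Working it through.** **Inputs, all from Secondary Behavioural Outcomes:** eight items; lowest rating 1; highest rating 3, 4 or 5 depending on the item; 0 for an item that does not apply or cannot be answered; total 0 to 31; low is good. The text does not name the instrument that has eight items. I take it to be the I-ADL, because the direction is stated in terms of instrumental activities and the 0-to-30 range is then given for the other test.

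**1. Reproducing the stated range.**
- Maximum: eight item maxima chosen from 3, 4 and 5 can sum to anything from 8 × 3 = 24 to 8 × 5 = 40. One set that gives 31 is 3 + 3 + 3 + 4 + 4 + 4 + 5 + 5. The upper limit is therefore consistent with the item ranges.
- Minimum: if every item is rated, the lowest total is 8 × 1 = 8. A total below 8 needs at least one 0 in the sum, and a total of 0 needs eight. The stated lower limit is therefore reachable only if zeros are added as scores.

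**2. Effect on the level of the score.** With k items coded 0 and the other 8 − k at the best rating, the total is 8 − k.

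| Items coded 0 | Total | Fully independent, all items rated |
|---|---|---|
| 1 | 7 | 8 |
| 2 | 6 | 8 |
| 4 | 4 | 8 |
| 8 | 0 | 8 |

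More generally, if the rated items carry e points above 1 in all, the total is (8 − k) + e. This is below 8 whenever e < k. When e ≥ k the total is no longer better than full independence, but the items coded 0 still pull it downwards.

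**3. Effect on change.** An item rated r at baseline and coded 0 at 12 months changes the total by 0 − r = −r. Since r runs from 1 to 5, the false improvement is 1 to 5 points per item. The upper end applies only to items already at their worst rating:

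| Item maximum m | Worst rating to 0 | Worst rating to full independence (1 − m) |
|---|---|---|
| 3 | −3 | −2 |
| 4 | −4 | −3 |
| 5 | −5 | −4 |

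Losing the rating is thus rewarded by one point more than full recovery.

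An item coded 0 at both visits adds nothing to the change. An item that is 0 at baseline and rated at 12 months raises the total by its rating. A participant who starts a medicine and handles it with full independence would be recorded as 1 point worse.

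**4. Worked example within the stated ranges.**
- Baseline: eight items rated 2, total 8 × 2 = 16.
- 12 months: four items rated 3 and four coded 0, total 4 × 3 + 4 × 0 = 12.
- Recorded change: 12 − 16 = −4, a 4-point improvement, although no rated item improved and four got worse.

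**The case against.** **The wording could describe a missing-value code.** The text calls 0 a none score, and the sentence follows the total range and speaks of questions in the plural. It might mean only that a total of 0 is not a valid score. That does not rescue the rule. The medication example assigns the 0 to a single item and calls it the score, and a total range starting at 0 cannot arise if such items are left out.

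**Zeros may be few.** Appendix D tells the tester to probe until an answer fits one of the boxes. The trial also aims at early disease, in people living at home who can complete questionnaires. This stands as a reason to expect fewer zeros from unclear answers. It does not help with items that do not apply.

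**The route from decline to zero is partly inferred.** The only item-level example is a patient who uses no medication, which is non-applicability and not lost ability. The response options are not shown, so an activity taken over by others may have its own dependence rating. This stands. What the text does say is that being unable to answer gives a 0.

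**Stronger readings are tempting.** A reader might infer that a definite share of true decline disappears, that each affected item gives 3 to 5 points, or that a group difference reverses. The documents support none of these. A share of lost decline needs a frequency of zeros, which is not given. The 3 to 5 points hold only for items at their worst rating at baseline. Reversal would need more zeros in one arm than in another, and nothing in the protocol establishes that.

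**Proration is usually left to the analysis plan.** True of the formula. The conflict itself lies in the item range, the meaning of 0, the total range and the direction, all of which the protocol fixes.

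**Conclusion.** The scoring rule is wrong as written and should be corrected. Zeros for unrated items enter a sum in which low is good, so each counts as better than full independence, and a rating lost between visits is recorded as an improvement of 1 to 5 points per item. This follows from the protocol's own figures; the only assumption is that the eight-item description belongs to the I-ADL.

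The size and direction of any effect on comparisons between arms cannot be computed, because neither the frequency of zeros nor their spread over the arms is given. The outcome is secondary and exploratory, and neither the primary tests nor the sample size depends on it. The correction matters for the reading of this one functional outcome, not for the trial's main conclusion.

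**What to change.** 1. State that 0 is a code for missing or not applicable and is never added as a score. Give the range for eight rated items as 8 to 31.
2. Record at testing whether a 0 means not applicable or cannot answer. The single code does not preserve this.
3. Compute the total from rated items, with a minimum number of them, using a proration that gives full independence the same score whichever items are rated. One way is to rescale each item as (rating − 1)/(maximum − 1) and average. If the familiar range is wanted, use 8 + 23 × average, where 23 = 31 − 8. A variant is 8 + 23 × Σ(rating − 1)/Σ(maximum − 1) over rated items; with all eight rated the denominator is 31 − 8 = 23, so it returns the ordinary sum.
4. Do not divide ratings by the item maximum. With assumed maxima 4, 3, 4, 4, 3, 5, 3, 5 (sum 31), the reciprocals sum to 3/4 + 3/3 + 2/5 = 2.15, so a fully independent person would score 31 × 2.15/8 = 8.3. With only five-level items rated the score would be 31/5 = 6.2, and with only three-level items 31/3 = 10.3.
5. Add a sensitivity analysis in which an item rated at baseline but unanswerable at 12 months takes its highest-dependence value. Proration alone leaves out the items that were lost, so it can still hide decline.

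In the worked example, each item still rated at 12 months has the rescaled value 2/(m − 1), at least 2/4 = 0.50. The baseline average of 1/(m − 1) would reach 0.50 only if all eight maxima were 3, which sum to 24 and not 31. The prorated score therefore records a worsening whichever four items are lost.

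The cost is one extra mark on the form for each 0, a revised scoring paragraph, and one more analysis. No new assessment is needed. For participants already tested, the reason for a 0 can be separated only if it was noted at the time.

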## Secondary Neuroscientific Outcomes

Title: Integrity of fibre tracts

Description: Changes in the integrity of fibre tracts can be measured by Diffusion Tensor Imaging (DTI).

Time frame: Testing before randomisation and after 12 months of intervention.

Test: DTI can be used to look at the loss of fibre rays in the hippocampus, which we assume to be stronger in the other intervention groups compared to the music group. DTI also sees several biomarkers in AS, which correlates with boiler-like functions (Nir et al., 2013).

Title: Plasticity changes in the brain's morphography

Description: Voxel-based Morphography on Structural MRI, it is possible to look at differences in hippocampus, functions in the default mode network (DMN), and how music archives the brain in the default mode network. As well as functional contexts on the groups before and after intervention.

Time frame: Testing before randomisation and after 12 months of intervention.

Test: In early stages of AD, the activity of the posterior part of DMN will begin to degenerate, while in the anterior and ventral networks, activity will increase (Damoiseaux, Prater, Miller, & Greicius, 2012). We want to watch DMN with silence and a choice of various music pieces (selected by participants; see Appendix C), and see if degeneration will slow down with music intervention.

## Other Measures

Tertiary outcomes will look at the differences within groups and of participants.

Title: Musical background

Description: Profile of Perception of Music Skills (PROMS) 15 minutes versions

Time frame: Testing before randomisation

Test: PROMS investigate musical skills. People with strong musical connection may prefer music intervention, but also get more out of a music intervention. Individuals are different and normally distributed in their musical abilities; it is interesting to see if music intervention for example will help better for those with stronger musical skills than those with less. It will be important for future research and treatment to know. If a person is not musical, training might be a better intervention.

Title: Physical shape

Description: Short Physical Performance Battery (SPPB)

Time frame: Testing before randomisation

Test: The Short Physical Performance Battery is a test that is used to screen physical function among elders. The test was developed to be used on people over the age of 65 years. The test has predication values for death and when people will have to move to a nursing home (Guralnik JM, 1994). The test evaluates balance and walking speed.

Title: Background

Description: General questionnaire about gender, music background, training habits and education

Time frame: Testing before randomisation

Test: We will ask about the general background of our participants. As gender, age and education. But we also want to ask about music backgrounds and training habits. We have used some of the parts from the Montreal Battery of Evaluation of Amusia (MBEA) that ask for music backgrounds and music experience. We also ask participants about the type of interference they prefer, not because they can choose, but then we may get a pointer about why someone will drop out of the study.

Title: Midway evaluation of therapy

Description: A questionnaire about therapy and Working Alliance Inventory, Short Revised (WAI-SR).

Time frame: after 6 months of intervention

Test: We will ask about how the therapy is working, and how much participants practice on their own. This test will be to assess fidelity of both therapists and participants. WAI-SR will be used to evaluate how well the therapist works with the participants. If the relationship is poor, changes may be done.

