### **Eligibility Criteria**

All adults with AD, above the age of 18, of any gender, are eligible to participate. In addition to having a diagnosis of AD, participants must live at home (not in a residential aged care facility, however they may have plans to move to such a facility in the future) and be able to give informed consent for the study. They also need to be able to complete questionnaires in Norwegian, to undergo magnetic resonance scans, and to attend intervention and assessment sessions in the area of Bergen, Norway. Participants can be non-musicians, amateur/hobby musicians, or professional musicians.

If participants move to a nursing home during the intervention period, they will not be excluded. All participants randomised will be retained and analysed, according to the intention-to-treat principle (see Statistical analyses).

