## **Statistical Methods**

All primary analysis will be conducted in the modified intention-to-treat population, i.e. all who were randomised and for whom outcome data are available will be analysed in the group to which they were randomised, regardless of whether they received the full intended intervention. All continuous variables will be screened for normality of distributions. If normality is confirmed, the three interventions will be tested in an overall test (one-way ANOVA with three levels), followed by multiplicity-adjusted post-hoc t-tests (as described in Statistical analyses below). However, only one comparison – music intervention versus standard care – is regarded as the primary comparison. Multiplicity adjustment is made for the two primary outcomes, leading to a two-sided 2.5% significance level. All other comparisons and outcomes are regarded as exploratory secondary and are not multiplicity-adjusted (i.e. will be tested on a two-sided 5% level). Additional sensitivity analyses will be conducted on the per-protocol population (by treatment received). Subgroups such as gender, education will also be investigated. Adjusted measures will be music aptitude at baseline. Working alliance will be examined as a mediator variable of later clinical outcomes.

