## **Project Management and Time Line for the Project**

Project start: 1. March 2018

Data retrieval of pre-scanning, pretesting and similar before intervention: 01.02.2018 – 01.06.2018

Recruitment will be continuous until we reach our goal. Recruitment will start in March 2018.

Initiation of intervention will also be continuous and start as each participant is scanned and tested. Scanning and testing will be done from March until June, or longer if necessary.

Intervention period: 01.03.2018 – 01.03.2019

The intervention period may vary for the different participants, but not the length, which will last for 12 months. This means that if a participant joins the project on June 1, 2018, the intervention will begin from that date and last for 12 months from that date.

Analysis of brain imaging data: 01.02.2018 to 01.02.2020

Analysis of imaging data will occur on a continuous basis after each participant has been in the scanner and taken the psychological tests. Since this is to be done twice, it is assumed that much time will go for analysis. Statistical analysis comparing data between interventions will not commence before the end of data collection and preparation (database lock) for all participants.

Article writing and publishing of results: 01.02.2020 to 01.02. 2021

During this period, the project team will work on preparing data for publishing, creating guidelines/manuals for interventions that can be used by the municipality and the rest of the country. The intervention material, such as the music, the music program, the exercise program, will be made available for all who wish to use it, both domestic and internationally.

Recruitment end: 01.01.2020

Recruitment will be an ongoing procedure until we get 135 participants or the project run out of time. Hence the last day of recruitment will be a bit before a year is left of the project so that participants still get the 12 months of intervention and the analysis can be included.

Project end: 01.02.2021

Around the end of the project we wish to send out an evaluation form for participants where we ask if they are still home and whether they have moved into a nursing home. We will also ask if we can contact them two and a half years after intervention (which will be before the project ends) and then again 5 years after end of intervention.

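### The living-at-home outcome has no category for death, so the nursing-home comparison is made among survivors; using baseline SPPB as a covariate would be an optional gain in precision

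*Protocol*

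**What the plan says.** Under Secondary Behavioural Outcomes, the outcome on living independently at home is described as "A measure of when people with AD move to a nursing home". It is collected by a question: after 12 months of intervention "we will ask our participants if they are still living at home or at a nursing home", and the team will "follow up with them after two and a half years and after five years to ask the same question". The Project Management and Time Line section describes an evaluation form for participants around the end of the project in which "we ask if they are still home and whether they have moved into a nursing home". It also says that permission will be sought for the later contacts. Neither section gives a third answer, a proxy respondent or a check of vital status.

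Under Other Measures, the SPPB is taken before randomisation, and the protocol says: "The test has predication values for death and when people will have to move to a nursing home". In Statistical Methods the only adjustment named is this: "Adjusted measures will be music aptitude at baseline". By the Eligibility Criteria "participants must live at home", so the outcome has no baseline value of its own. The analysis set in Statistical Methods, stated for the primary analyses, is "all who were randomised and for whom outcome data are available will be analysed in the group to which they were randomised". The same section makes all outcomes other than the two primary ones exploratory.

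**The concern.** A two-answer question put to the participant fails for anyone who has died. Unless something further is done, deaths end up with the people who could not be reached, and the proportion at home is calculated among those still alive. Survival is a post-randomisation event, so the groups compared are no longer the randomised groups. If one arm has fewer deaths, its survivors may include frailer people who are more likely to be in a nursing home. That arm can then look worse on residence although no fewer of its members are alive and at home.

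This matters because Specific Objectives names keeping people with AD at home for as long as possible as the goal of the project, and this outcome measures it. The gap also lies in data collection: a later analysis plan cannot classify deaths at 2.5 and 5 years that were never recorded.

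A smaller matter concerns the SPPB. The protocol calls it prognostic for this event and collects it at baseline, but gives it no role in the analysis. Music aptitude, the one adjustment named, is nowhere linked to nursing-home entry.

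**Working it through.** **The plan's own figures.** No figure is given for this outcome. The sample size rests on the primary comparison: d = 0.7, two-sided 2.5%, 80% power, 40 per group. A t-test calculation gives 40.08 per group, and power 79.9% at 40, so the figure reproduces. Recruiting 45 allows for 1 − 40/45 = 11.1% attrition. The check below uses 45 per arm.

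**Inputs that the protocol does not give.** Death rates, nursing-home rates and the strength of the SPPB association are all assumed.

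**Effect of counting survivors only.** Let D be the proportion dead and h the proportion of all randomised who are alive and at home. The survivor-only proportion at home is h / (1 − D).

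| Dead, control vs music | Alive at home among all randomised | At home among survivors | True difference | Survivor-only difference |
|---|---|---|---|---|
| 5% vs 5% | 80% vs 80% | 84.2% vs 84.2% | 0 | 0 |
| 10% vs 5% | 80% vs 80% | 80/90 = 88.9% vs 80/95 = 84.2% | 0 | −4.7 points |
| 40% vs 30% | 20% vs 20% | 20/60 = 33.3% vs 20/70 = 28.6% | 0 | −4.8 points |
| 40% vs 30% | 36% vs 36% | 36/60 = 60.0% vs 36/70 = 51.4% | 0 | −8.6 points |
| 40% vs 30% | 30% vs 35% | 30/60 = 50% vs 35/70 = 50% | +5 points | 0 |

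Unequal deaths can thus produce a gap where none exists (rows 2 to 4) or remove a real one (row 5). With equal deaths and equal alive-at-home shares nothing arises (row 1). For scale, in row 4 the survivors number 45 × 0.60 = 27 and 45 × 0.70 = 31.5. The standard error of the survivor-only difference is then √(0.600 × 0.400/27 + 0.514 × 0.486/31.5) = 0.13, or 13 points. The shift is systematic, but in one trial of this size it is smaller than one standard error.

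**Leaving out the SPPB.** The chance difference in mean SPPB between two arms of 45 has standard deviation √(2/45) = 0.21 SPPB SDs, with a 95% range of ±0.41. A simulation with no treatment effect (20,000 trials per setting, event rates 15% and 40%, SPPB odds ratio 1.5 to 3 per SD) gave for the unadjusted comparison:

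- bias of at most 0.001;
- type I error of 4.9% to 5.6%;
- 2% to 18% of the variance of the difference explained by SPPB imbalance.

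Power for an assumed treatment odds ratio of 0.3, unadjusted then adjusted for SPPB (4,000 trials per setting):

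| Event rate | SPPB odds ratio per SD | Unadjusted | Adjusted |
|---|---|---|---|
| 50% | 2 | 67.7% | 72.4% |
| 50% | 3 | 60.0% | 69.1% |
| 30% | 2 | 54.6% | 57.5% |

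The gain is about 3 to 9 points in these settings, and almost nothing at an SPPB odds ratio of 1.5.

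**The case against.** **The protocol nowhere says that the dead are left out.** The available-data rule in Statistical Methods is written for the primary analyses, and Eligibility Criteria says that everyone randomised is kept and analysed. A reader might infer that the available-data rule removes deaths from this outcome, but the text does not go that far. What stands against the plan is narrower. The only collection method given cannot return an answer for someone who has died, so the promise to analyse everyone cannot be kept for this outcome as it is collected. Adverse-event recording may capture deaths during the intervention, but it is not extended to 2.5 or 5 years.

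**Chance differences in frailty.** A reader might also infer that these distort the comparison because randomisation is not stratified and SPPB is not adjusted for. They do not. Under concealed randomisation such imbalance is part of the sampling error that the unadjusted test already covers, as the type I error near 5% shows. Nor is the SPPB the only baseline predictor available: age, MMSE and I-ADL are collected too. Covariates for an exploratory outcome may properly be left to an analysis plan that is not shown. This objection stands, and it reduces the SPPB to an optional improvement.

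**A reversed result.** The examples show a spurious gap arising from equality, or a 5-point gain disappearing. None turns a true benefit into apparent harm. The unequal cases assume mortality differences of 5 to 10 points, for which the protocol gives no basis.

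**A composite changes the question.** The protocol speaks of when people move, and a yes/no status at fixed dates is a different quantity. This is fair. If move dates are collected, time to nursing home with death as a competing event stays closer to the stated aim.

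**Conclusion.** The concern holds as a gap in the definition and collection of one exploratory secondary outcome. The protocol names death beside nursing-home entry as something the SPPB predicts, follows people for up to 5 years, and offers no way to record that a participant has died. Followed as written, this gives a survivor-only comparison.

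On the assumed rates, mortality differences of 5 to 10 points shift the comparison by 4.7 to 8.6 percentage points. The shift is zero when deaths and alive-at-home shares are equal. It is likely small at 12 months and larger at 2.5 and 5 years. These figures illustrate the mechanism and do not predict what the trial will show.

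The unused SPPB is a loss of precision and not an error: roughly 3 to 9 points of power at an assumed odds ratio of 2 to 3 per SD, and almost none at 1.5. The primary outcomes and the sample size are unaffected.

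**What to change.** 1. In Secondary Behavioural Outcomes and in the Time Line section, define the outcome among all randomised, at each time point, as alive and living at home: yes or no. Count death as no, and report deaths and nursing-home moves separately by arm. If dates of moves are collected, time to nursing home with death as a competing event is an alternative.
2. State that residence and vital status are obtained from a contact person when the participant cannot answer.
3. Optionally, in Statistical Methods, name baseline SPPB total as a covariate for this outcome, beside music aptitude.

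The cost is wording plus one question to a contact person, since the SPPB is already collected. There are three downsides: the composite can be read only with its components shown, the model gains one parameter, and the SPPB-adjusted odds ratio is conditional and so not directly comparable with an unadjusted one.
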